**Methods:**

This is a prospective longitudinal cohort study of adult (≥18 years) acute medical hospital admissions with nested health economic and situation analysis in four hospitals: 1) Queen Elizabeth Central Hospital, Blantyre, Malawi; 2) Chiradzulu District Hospital, Malawi; 3) Hai District Hospital, Boma Ng’ombe, Tanzania; 4) Muhimbili National Hospital, Dar-es-Salaam, Tanzania. Follow-up duration will be 90 days from hospital admission. We will use consecutive recruitment within 24 hours of emergency presentation and stratified recruitment across four sites. We will use point-of-care tests to refine estimates of disease pathology. We will conduct qualitative interviews with patients, caregivers, healthcare providers and policymakers; focus group discussions with patients and caregivers, and observations of hospital care pathways.

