### Objectives

The primary objectives of this mixed methods (clinical, health economics and qualitative) study are:

*Clinical:* Determine the prevalence of multimorbid disease in adults admitted to hospital with acute medical conditions in Malawi and Tanzania.

*Health Economic:* Measure economic costs incurred and changes in health-related quality of life between admission and 90 days post admission.

*Situation analysis:* Describe current care for multimorbidity, enabling and hindering factors to the delivery of patient centred care.

We aim to use the findings to inform the development and design of a randomised controlled trial.

The secondary objectives are:

*Clinical:*

1.Measure prevalence of important pre-selected individual conditions, including chronic non-communicable (hypertension, diabetes mellitus and chronic kidney disease) and communicable (HIV infection) conditions.2.Measure hospital readmission rate 30 and 90 days after admission.3.Measure survival 30 and 90 days after admission.4.Measure a composite of readmission free survival 30 and 90 days after admission.5.Measure markers of disease control 90 days after admission.6.Measure the rate of end-organ damage (such as cerebrovascular accident and myocardial infarction).

*Health Economic:*

1.Disaggregate economic costs from patient and health system perspectives and sub-analyse according to the presence of multimorbidity and other socio-economic factors.2.Model how patients with different multimorbidity incur costs as they pass through the health system.3.Analyse changes in Health-related Quality of Life according to presence of different diseases.4.Estimate the potential cost-effectiveness of a selected intervention to improve diagnosis and treatment for people with multimorbidity.

*Situation Analysis:*

1.Describe healthcare pathways for adults during and after acute medical admission using structured observational data during patient admission.2.Qualitatively describe (i) patients’ level of health literacy related to their own conditions and (ii) healthcare engagement for patients with multimorbidity using key-informant interviews.

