### Variables

**
*Phase 1 A: Prospective longitudinal cohort study*.** The main outcome is to define the characteristics of multimorbidity. We will employ enhanced point of care test (POC) diagnostics for patients admitted to the study to determine the prevalence of multimorbid diseases of interest (specifically HIV, hypertension, diabetes and chronic kidney disease). All POCs used in the study are CE marked and commercially available. We will make the results of these tests available to treating healthcare providers using a standardised proforma. No treatment recommendation will be provided with this information and clinicians will be able to interpret and use this information independently. Structured data extraction of clinical information (including potential predictors of patient outcomes) will be performed at intervals (described in
Table 1 from patient records.

**
*Phase 1 B: Health economic evaluation*.** To explore the impact of socioeconomic status (SES) on patient costs, clinical outcomes and health-related quality of life (HRQoL) we will calculate wealth scores and use these to assign all clinical cohort study participants to SES quintiles. For participants randomised to the health economic study, we will collect data on patient costs at admission (in person), discharge (in person), 30 and 90 days post discharge (in person or by telephone). Health system costs for patients in the cohort study will be modelled using top down and bottom up costing methods. HRQoL will be estimated in quality adjusted life years (QALYs).

**
*Phase 1 C: Situation analysis*
** In depth interviews (IDI) and focus group discussions (FGD) with patients recruited to the cohort study, and their care givers will be conducted to understand their experiences, preferences, and priorities, including level of health literacy and engagement with healthcare providers for long term management of chronic conditions. Exploration of detailed experiences from patients and carers will provide specific concrete examples of their expectations, and any concerns they have, as well as their priorities and perceptions of how the hospital currently manages acute medical patients with multimorbidity, problems and how best to address them.

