Other conditions are expected to contribute to multimorbidity, for example hearing and visual impairment, causes of impaired mobility such as injury at birth, or disability from trauma, surgical procedures and others later in life. A key criterion for inclusion in the planned intervention study will be potential for improved morbidity or mortality from linkage to care. We will therefore collect data on disability using standardised questionnaires, with key components from Washington Group on functioning, Patient Health Questionnaire (PHQ)-9 for depression in addition to data tools used in previous cohort studies for the collection of standardised clinical information, and allow this to inform the intervention design.

Clinical outcomes, coded from a structured case summary and the available medical notes, will be established as follows:

1.Medical diagnosis and supporting evidence.2.In-patient treatment of these diagnoses, including time of appropriate treatment establishment.3.Vital signs, including pulse oximetry (using a A310 finger oximeter), respiratory rate, pulse rate, blood pressure and temperature.4.Routine laboratory data supporting these diagnoses (such as urine lipoarabinomannan [LAM], serum CrAg).5.Clinical outcomes will also be ascertained at hospital discharge, 30 days and 90 days as:6.Death (coded from all available records).7.Readmission to hospital.

Data will be collected by a study nurse using electronic data capture. This will describe the patient characteristics, medical history and ‘patient journey’ through the healthcare system. Age, date of birth and sex will be documented from patient reports and/or clinical notes. To ensure complete data collection, we will prospectively collect data on vital signs, details of resuscitation, medication administration, results of clinical, laboratory, and radiologic examinations. All clinically relevant findings will be entered into the medical notes to ensure availability to the responsible clinicians.

As a component of the functional assessment, we will measure hand grip strength at day 90 follow-up using a GRIPX Digital Hand Dynamometer, which is a known predictor of health and overall strength
^
28
^. Grip strength will be measured seated on a chair without elbow rests, with the elbow loosely flexed at 90
^0^, and the wrist in a neutral position
^
29,
30
^. Grip strength will be measured as the mean of three tests on both hands with 60 seconds of recovery between each attempt.

**

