### Analysis

**
*Phase 1 A: Prospective longitudinal cohort study - quantitative statistical analysis*.** We will report the study in accordance with STROBE guidelines. A CONSORT diagram will summarise participant enrolment and follow-up. We will report descriptive statistics, including N (sample size of analysis population), n (sample size of analysis population without missing values). For continuous data we will report the mean and standard deviation for normally distributed data, or median and interquartile range for data that are not normally distributed. The proportion of observed levels will be reported for all binary and categorical measures alongside corresponding exact, binomial exact 95% confidence intervals (CIs) for proportions when appropriate. Results will be disaggregated by sex. Where appropriate, we will use multiple imputations using chained equations for missing data.

Will provide in-depth baseline epidemiologic and clinical management data across the different sites. Similarities and differences across sites will be recorded. Analysis will include evaluation of the association between clinical management and patient outcomes. Univariate and multivariate strength of association between variables and patient outcomes will be tested by logistic regression modelling.

Prevalences will be given as a proportion with 95% confidence intervals of the population estimate. Combinations of more than one will be assessed for their “joint prevalence” in order to understand multimorbidity disease clusters.

**
*Phase 1B: Health economic*.** Principle components analysis (PCA) will be used to construct wealth scores using individuals’ asset and other data, and wealth quintiles in the study population. Additionally, participants will be assigned to quintiles in reference to most recent DHS survey, allowing socioeconomic assessment of the study population relative to the national population.

Patient costs will be estimated for each individual patient including any costs incurred by their guardians in accompanying them to hospital or subsequent health care visits. Indirect costs (

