### Data management

Consent will be documented on paper or electronic forms. A paper copy will be given to the participant or guardian, and any original paper will be stored in a locked cabinet at the local hospital site, accessible only to the study team. All study data will be collected electronically.

Baseline, follow-up questionnaire data, and physiological observations (including pulse, respiratory rate, blood pressure, and oxygen saturations), and any point-of-care measures will be captured direct to Open Data Kit
^
32
^ software on devices with password encryption.

Clinical information including presenting complaints, history of presenting complaints, past medical history and drug history will be collected. Data on differential diagnosis and final diagnosis will be collected including clinical actions (
*e.g.*, prescribed medication) and patient response. We will also collect information on prescribed medication at hospital discharge, including where possible out of pocket expenses, health literacy and drug dispensary access (including stock outs).

Laboratory test results will be directly electronically exported from laboratory information systems where possible.

The study will adhere to LSTM (sponsor) data management and security policies, and encryption guidelines. This allows the data from each site to be collated, and presented at summary level in near real-time for the purposes of monitoring recruitment across both countries. During the study, individual participant level data will be available by the study team only, for the purposes of data validation and completeness checking. Access to this will be controlled by the same data security policies, with journaling of data change requests to allow full data audit.

After successful import of external data, and formal closure of the study, data will be fully anonymised by removing identifiers (including embedded electronic data) and granulating data which might enable an individual to be triangulated (area of habitation will be retained at “ward” level, and age rounded to the nearest year).

Data management for the patient costs, and HRQoL will be as per the clinical cohort study. Health system cost data will be collected and stored in custom built Excel spreadsheets.

**

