## Limitations

There are a number of limitations with this study, which we have attempted to mitigate. First, there are a limited number of sites in two countries. In order to generate broadly generalisable results, the chosen sites reflect a mix of tertiary / referral hospitals and district hospitals in each country. Second, we have decided to systematically screen for four conditions (HIV, hypertension, diabetes and CKD) using point-of-care diagnostics. This may miss multimorbidity from other chronic conditions, which require additional infrastructure to confirm diagnoses (such as clinical imaging or enhanced laboratories), but we will collect clinical data on all diagnosed chronic conditions. A recent systematic review indicates a high burden of disease from these four conditions among hospitals patients, which can importantly be diagnosed using available point-of-care tools
^
24
^. Third, CKD diagnoses require evidence of chronicity of disease at three months and therefore data in this condition is prone to survivorship bias. Fourth, EQ5D-5L data and resulting QALY estimates may not reflect the most accurate picture of HRQoL in our study context. However, through our eCRF, we will collect rich clinical data with additional scales (such as the Patient Health Questionnaire-9 [PHQ-9] screening tool for depression
^
34
^; and clinical frailty scale
^
35
^ to explore the possible limitations and interrelationships. Fifth, our planned situation analysis will provide a cross-sectional picture of the health system at the time of the study, which is not able to incorporate the dynamic and adaptive nature of health systems. However, the MultiLink consortium includes researchers from each country and site, with a rich understanding of the context.

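### Logistic regression is the only model named for relating clinical management to outcomes at fixed times from admission, so care received after admission is exposed to immortal-time bias

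*Protocol article*

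**What the plan says.** The protocol article's Analysis section (Phase 1 A) sets the aim: "Analysis will include evaluation of the association between clinical management and patient outcomes". The model follows at once: "Univariate and multivariate strength of association between variables and patient outcomes will be tested by logistic regression modelling". No other model is named for Phase 1 A outcomes.

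Three places show that the exposure builds up after admission:
- Data sources and measurement lists "In-patient treatment of these diagnoses, including time of appropriate treatment establishment".
- Variables says "Structured data extraction of clinical information (including potential predictors of patient outcomes) will be performed at intervals"; Table 1 schedules visits at days 0, 2, 5 and 7, at discharge, and at days 30 and 90.
- Data management adds "We will also collect information on prescribed medication at hospital discharge".

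The outcome clock starts at admission. The abstract's Methods says "Follow-up duration will be 90 days from hospital admission", and the secondary clinical objectives place readmission, survival and their composite at day 30 and day 90 from admission.

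The Analysis section mentions no landmark, no time-dependent exposure and no restriction to predictors known at admission. Limitations recognises survivorship for one condition only: "CKD diagnoses require evidence of chronicity of disease at three months and therefore data in this condition is prone to survivorship bias".

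**The concern.** Time zero is admission, but treatment starts later. Whoever ends up treated was, by definition, still alive and in hospital when treatment began. Whoever died first is untreated whatever the treatment would have done. A logistic model for death by day 30 or day 90 with received or not received as a covariate compares these two groups directly and reads the survival time needed to be treated as an effect of treatment. Early discharge works the other way: patients well enough to leave quickly also miss treatment and mostly survive.

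Discharge medication is the extreme case. No patient who dies in hospital can have it, so in a model that includes all admissions every in-hospital death falls in the unexposed group.

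The study is meant to inform a complex intervention and a later cluster randomised trial. An association between in-patient care and survival that arises only from timing could make an element of care look more useful, or less useful, than it is.

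**Working it through.** The plan states no figure for this analysis, so there is none to reproduce. The documents give no mortality, length of stay, treatment delay or uptake. All inputs below are assumptions, and the true treatment effect is set to nil, so a correct analysis should return 1.

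**Set-up 1: death only, no discharge.** 90-day mortality 20% to 40%; 70% of patients due to be treated if they live long enough; exponential delay to treatment; 1,000,000 simulated patients per scenario. Odds ratio for 90-day death, ever treated against never treated:

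| Median delay | Mortality peaking early (Weibull shape 0.5) | Constant hazard |
|---|---|---|
| 0.25 day | 0.80 to 0.81 | 0.98 |
| 1 day | 0.65 to 0.68 | 0.93 to 0.94 |
| 3 days | 0.50 to 0.53 | 0.83 to 0.84 |
| 7 days | 0.36 to 0.39 | 0.66 to 0.68 |

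Reading one cell (20% mortality, 1 day, early peak, odds ratio 0.68): about 70% of survivors are treated, odds 0.70/0.30 = 2.33. The odds among those who died are 0.68 × 2.33 = 1.59, that is 1.59/2.59 = 61% treated. The nine-point gap arises only because some patients died before their treatment was due. With treatment made time-dependent, the rate ratio is 0.99 to 1.01 in every scenario.

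**Set-up 2: discharge also ends the chance of treatment.** 20% die, all in hospital, with exponential time to death (median 3 or 5 days). Survivors stay 6 days on average. Treatment start is exponential with median 0.5, 1 or 1.5 days. These cases can be done by hand.

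*Everyone due to be treated.* Odds of being treated before death = median time to death / median start.
- Exponential stay: median stay = 6 × ln 2 = 4.16 days, so the odds among survivors are 4.16 / median start. The start time cancels and the odds ratio is 3/4.16 = 0.72 or 5/4.16 = 1.20.
- Gamma stay (shape 2, mean 6, so scale 3): odds among survivors = (1 + 3 ln 2 / median start)² − 1.
  - Start 0.5 day: 5.159² − 1 = 25.6. Odds ratios 6/25.6 = 0.23 and 10/25.6 = 0.39.
  - Start 1 day: 3.079² − 1 = 8.48. Odds ratios 3/8.48 = 0.35 and 5/8.48 = 0.59.
  - Start 1.5 days: 2.386² − 1 = 4.69. Odds ratios 2/4.69 = 0.43 and 3.33/4.69 = 0.71.

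*Only 70% due to be treated.* Multiply each treated proportion by 0.7 before forming odds.
- Gamma stay: 0.64 to 0.86.
- Exponential stay: 0.83 to 1.10. For example, median death day 5 and start 1.5 days: deaths 0.7 × 5/6.5 = 0.538, odds 1.167; survivors 0.7 × 4.16/5.66 = 0.514, odds 1.06; ratio 1.10.

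**Remedy check.** Restricting to patients alive and in hospital at 48 hours, with exposure defined by what had started by then, returned about 1.0 in every scenario.

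**The case against.** The strongest reply is that the article never says that treatment ever received will be entered as a fixed covariate. Recruitment is within 24 hours of presentation, treatment start time is to be recorded, and management could be coded as care at or near admission or analysed in a landmark set. A full analysis plan may settle this. That stands, and it is why the point is worded as an exposure to bias. What remains is that the article goes beyond silence: it names the model, names clinical management as the exposure, and acknowledges survivorship only for CKD.

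A second reply is that the size is fragile. That also stands. A reader might infer that this analysis makes any treatment look protective. The working does not support that: with an exponential stay and median death at day 5 the odds ratio is 1.20, because early discharge also prevents treatment. The lowest values, 0.23 to 0.43, need everyone to be due for treatment, a gamma-shaped stay and median death at day 3. With near-immediate treatment and a flat hazard the bias is negligible (0.98).

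A reader might also infer a parallel error in readmission, because the objective reads "Measure hospital readmission rate 30 and 90 days after admission": that patients who die in hospital are counted as not readmitted. The documents do not say so. The denominator is not stated, which is ordinary content for an analysis plan. Moreover, with complete follow-up, readmission per admitted patient with deaths kept in the denominator is a valid cumulative incidence with death as a competing event. If in-hospital mortality were 15% and 30%, and readmission among those discharged alive 15% and 20%, the per-admission figures would be 0.85 × 0.15 = 12.8% and 0.70 × 0.20 = 14.0%, ratio 1.10. The ratio among those discharged alive would be 0.20/0.15 = 1.33. These are answers to two questions, and neither is a biased version of the other. The readmission-free survival composite already counts death as an event.

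Finally, the only stated threshold for including a disease in the intervention is 5% prevalence, and no section makes a choice depend on a treatment odds ratio. That limits the consequence.

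**Conclusion.** The point holds in a limited form. The stated aim (management against outcome) and the only stated model (logistic regression at fixed times from admission) do not fit together for care that starts after admission, and least of all for discharge medication. If care received is used as a fixed covariate, an ineffective treatment can give an odds ratio anywhere from about 0.2 to 1.2, usually below 1. Where it falls depends on mortality timing, treatment delay, length of stay and uptake, none of which the documents give. Logistic regression on predictors known at admission is unaffected, as are the prevalence estimates and the descriptive survival and readmission figures. This is a worthwhile correction to a secondary analysis, not a flaw in the study's main result.

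**What to change.** Change the Phase 1 A analysis text as follows.

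1. Keep logistic regression for predictors known at admission.
2. For management delivered after admission, use either a landmark analysis (for example, patients alive and in hospital at 48 hours, exposure defined by what had started by then) or a Cox model with treatment as a time-dependent covariate. Account for site in both.
3. Analyse discharge medication only among patients discharged alive, with time counted from discharge.
4. Optionally, report readmission from discharge among those discharged alive as a supplementary estimate beside the planned rate from admission.

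The cost is wording and code. Treatment start time is already listed for collection, discharge has its own visit, and Study status says that code is still being developed and no analysis has been done. The Cox option also needs dates of death; the landmark option can keep a logistic model for status at day 30 or day 90. There are two drawbacks to state: a landmark drops early deaths and early discharges and so answers a narrower question, and neither method removes confounding by indication, since sicker patients may be treated sooner or differently.

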## Introduction

### Background and rationale

Non-communicable diseases (NCDs), which can be accelerated by human immunodeficiency virus (HIV) infection and its therapy, are a major health problem in sub-Saharan Africa (sSA)
^
1
^. Diagnosis is frequently delayed until emergency hospital presentation, when people are already severely unwell
^
2
^. In hospitals, unrecognised multimorbidity (“the co-existence of two or more chronic conditions”
^
3
^ results in frequent re-admission, high out-of-pocket expenses, disability and preventable death
^
4
^. In sSA, co-existent infectious and non-communicable disease pathology is common
^
5
^. Some studies suggest a higher burden of multimorbidity among females compared to males
^
6,
7
^. Existing risk stratification and screening frameworks from High Income Countries are poorly calibrated for people in sSA and underestimate severity. For example, diabetes and hypertension are more prevalent in African populations at younger ages
^
8
^. Acute medical admission is frequently the index presentation of multimorbid disease in areas of poverty
^
9
^.

The patient pathway in sSA regions may be protracted and complex
^
10
^. People frequently seek healthcare late for reasons including opportunity cost, poor health literacy and prior consultation with informal care providers. This leads to high prevalence of poorly controlled multi-morbid disease in hospital emergency care where recognition of multimorbidity is delayed or prevented by weak triage systems, resource limitations, and a focus on a single primary diagnosis
^
11
^. Commitments to Universal Health Coverage and the World Health Organization Model List of Essential Medicines
^
12
^ mean that HIV and NCDs are treatable through improved access to essential medicines. However, significant barriers include a lack of patient empowerment and health literacy, shortage of healthcare workers (HCW) and limited training
^
13
^.

Malawi (low income) and Tanzania (low-middle income) are neighbouring countries in the sub-Saharan African region that have experienced dramatic increases in life expectancy between 2000 and 2020 (Malawi 45.6 to 64.3 and Tanzania 50.8 to 65.5 years of age)
^
14,
15
^. This has been accompanied by increased rates of non-communicable diseases such as hypertension and type 2 diabetes, however, the health systems of both countries are currently weighted toward communicable disease control
^
16

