### Setting

This study will be conducted in four sites across two countries (Malawi and Tanzania). Within each country we will recruit patients from a central referral hospital and a district hospital to develop generalisable results, broadly applicable within both contexts. The study sites are: Queen Elizabeth Central Hospital, Blantyre, Malawi; 2) Chiradzulu District Hospital, Southern Region, Malawi; 3) Hai District Hospital, Tanzania; 4) Muhimbili National Hospital, Dar-es-Salaam, Tanzania. The study is planned to take approximately 15 months (12 months recruitment, with an additional three months to complete follow up) and will be conducted in parallel in all sites.

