*Phase 1 B: Health economic data sources and measurement*.** All consenting study participants will be asked asset ownership, house construction and demographic questions extracted from the most recent relevant national Demographic and Health Survey (DHS). Patient cost data will be captured before, during, and for 90 days after hospital admission using an amended version of the STOP-TB tool, a widely-used questionnaire for measuring TB patient costs
^
31
^. We will capture direct medical costs (
*e.g.*, drugs, diagnostics, consultation and inpatient fees), non-medical costs (
*e.g.*, food and transport), indirect costs (lost time for patients and guardians). Where a patient is readmitted to hospital, we will also capture these costs. Costs will be captured in local currency and presented in 2024 United States dollars.

Health system costs will be collected using top-down and bottom-up (micro) costing methods. We will develop and validate (with relevant hospital staff) a visual model of individual patient pathways through the study hospitals. This will be supplemented with data on waiting times, and time spent with various health workers from the sample of patients that are included in observations conducted as part of the situation analysis. Costs for each stage of the patient pathway (triage, admission, diagnostics, treatment, discharge, readmission
*etc*.) will be based on unit costs for tests, staff time, hospital bed days and other inputs, obtained from hospital data, tests and consumables suppliers, and Ministry of Health (MoH). Any other costs deemed relevant during the data collection stage will also be included. Top-down costing data on hospital overheads (utilities, building costs, maintenance,
*etc*.) will be obtained for each hospital.

HRQoL data will be collected using the EQ-5D-5L questionnaire in English, Chichewa (Malawi) and kiSwahili (Tanzania). The questionnaire will be administered, at admission, discharge, 30 and 90 days post admission in person or (day 30) by phone (as for patient costs).

**

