*e.g.*, lost time for paid or unpaid work, including housework) will be estimated based on the number of days of reported inability to work multiplied by the pre-disease wage given by patients during their baseline interview. The patient pathway model will be parameterised with unit costs and used to estimate individual patient and health system costs for a set of the most frequently observed multimorbidity combinations and patient types. Capital costs extending beyond one year will be annualised over their expected lifespan. Results will be presented as means and 95% confidence intervals. Deterministic and probabilistic sensitivity analyses will be conducted to test the robustness of the results. Multiple logistic regression will be used to compare patient costs by multimorbid condition(s) and wealth quintile to identify any significant differences. Additionally, we will examine the relationship between patient costs and age and sex. Change in HRQoL, expressed as QALYs, between admission, day 30 and day 90 interviews will be estimated using the area under the curve method. QALYs will be calculated according to the most relevant available tariff based on both geographical proximity and economic context. In our study we will use Uganda’s tariff for Tanzania, and Zimbabwe’s tariff for Malawi. Updated tariffs will be used if these become available before the analysis. The QALY calculations will also consider mortality during follow-up by attributing the lowest value from each value set (which corresponds to death), from the date of death until the end of the follow-up period. Missing patient cost or HRQoL data will be imputed using multiple chained imputations modelling with a predictive mean matching algorithm and relevant baseline variables.

Health economic analysis will be performed in Stata v15.4 and Excel.

**
*Phase 1 C: Situation analysis*.** Transcription and translation will be performed in line with local standard procedures. For accuracy, during the first 10 transcriptions a researcher will read the transcribed interviews and focus groups while listening to the audio recordings, and then check translations. Further checks will depend on the quality of these initial evaluations.

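### Wealth quintiles are defined in a two-country study population with no within-country rule, so if pooled, their contrasts on cost and QALYs are confounded with country

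*Protocol article*

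**What the plan says.** Under Variables, Phase 1B, the purpose is to explore how socioeconomic status affects patient costs, clinical outcomes and HRQoL. To that end, "we will calculate wealth scores and use these to assign all clinical cohort study participants to SES quintiles".

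Under Analysis, Phase 1B, principal components analysis gives wealth scores "and wealth quintiles in the study population". The next sentence adds a second version: "Additionally, participants will be assigned to quintiles in reference to most recent DHS survey". Its stated role is to place the study population against the national one, in the singular although there are two nations. Under Data sources and measurement, the asset and housing questions are "extracted from the most recent relevant national Demographic and Health Survey (DHS").

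The Setting section names four hospitals, two in each country. The Background gives the only economic contrast between the countries: "Malawi (low income) and Tanzania (low-middle income) are neighbouring countries".

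The Phase 1B analysis then compares patient costs by multimorbid condition and wealth quintile in a regression, and also looks at age and sex. It names neither country nor site, and does not say which version of the quintiles enters. For HRQoL, "In our study we will use Uganda’s tariff for Tanzania, and Zimbabwe’s tariff for Malawi". Costs are collected in local currency and shown in 2024 US dollars. Lost time is valued at each patient's own wage before illness.

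**The concern.** If one ranking is made across both countries and asset wealth differs between them, the bottom quintile holds more patients from the poorer country and the top quintile more from the richer one. Two of the outcomes to be compared across quintiles carry country by construction:

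- HRQoL is scored with a separate value set in each country.
- Costs rest on local fees and local wages. Converting to US dollars does not remove differences in those levels.

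A contrast between quintiles would then mix the effect of wealth within a country with the difference between countries. The analysis exists to isolate the former. At stake is the socioeconomic part of the health economic objectives; the primary prevalence estimates are not affected.

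**Working it through.** **The plan's own figure.** The documents state no figure for the quintile analysis itself. The one related number is the health economic sub-sample, which reproduces: 1600 / 3 = 533.3, and 533.3 / 4 = 133.3, against the stated figure of about 133 per hospital.

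**Inputs for the illustration.** All are assumptions, because the article gives no wealth distribution by country:
- two countries of equal size;
- asset scores normal with SD 1 in each, with means D apart;
- no effect of wealth within country;
- a constant tariff difference of 0.10 for the same health state.

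**Formulas.** The pooled cut points c1 to c4 solve 0.5 Φ(c) + 0.5 Φ(c − D) = 0.2, 0.4, 0.6, 0.8. The richer country's share of quintile k is p_k = 0.5 [Φ(c_k − D) − Φ(c_(k−1) − D)] / 0.2. The share of country variance explained by quintile is the sum over k of 0.2 (p_k − 0.5)² / 0.25.

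| D (SD) | Richer country, bottom quintile | Richer country, top quintile | Top minus bottom | Country variance explained |
|---|---|---|---|---|
| 0 | 50% | 50% | 0.00 | 0.00 |
| 0.2 | 43% | 57% | 0.14 | 0.01 |
| 0.5 | 33% | 67% | 0.34 | 0.05 |
| 1.0 | 18% | 82% | 0.63 | 0.19 |
| 1.5 | 8% | 92% | 0.84 | 0.37 |
| 2.0 | 3% | 97% | 0.94 | 0.53 |

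(Differences are from unrounded shares.)

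**Spurious HRQoL gap.** The top-to-bottom gap is the tariff offset times the difference in country share:
- D = 0.5: 0.10 × 0.34 = 0.034 in utility.
- D = 1.0: 0.10 × 0.63 = 0.063 in utility.

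The plan reports QALYs by area under the curve to day 90, and 90 / 365 = 0.247 years:
- D = 0.5: 0.034 × 0.247 = 0.008 QALY.
- D = 1.0: 0.063 × 0.247 = 0.016 QALY.

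The gap scales in proportion to the offset.

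**Spurious cost gap.** The documents give no cost difference between countries, so no money figure can be stated. By the same formula, the gap in mean cost between top and bottom quintile would be 34% to 63% of whatever the country difference in mean cost is, for D of 0.5 to 1.0. This holds for means and does not carry over directly to an odds ratio from the logistic model that the article names.

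**After the fix.** With quintiles cut within each country, every quintile has the same country mix by construction. That is the D = 0 row, and the artefact is zero.

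**The case against.** The strongest reply is that pooling is inferred. The article does not say that one score is built across both countries. Its two sentences contrast an internal reference with a national one and do not address pooled versus per-country cut points. Items drawn from each national survey would make per-country scores a natural choice. This stands in part: pooling is the plain reading of quintiles cut in the study population, but the text does not settle it, so the point is conditional.

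A second reply is that the level of the component analysis and the covariate list are details a condensed article may leave to the full protocol or SAP. This carries some weight, since the covariates named are not presented as a closed list. It does not dispose of the point. The article does state the population in which quintiles are cut and the terms of the cost comparison, and those two statements together produce the problem.

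A third reply is that the DHS-referenced quintiles are already planned. They are, and they would serve. But the article describes them as an addition for placing the sample against the nation and does not make them the exposure in the comparisons.

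A reader might infer that quintile would largely stand in for country. The documents do not support that. In the illustration, quintile explains more than half of the variance in country only at a gap of about 2 SD. The sole evidence of any gap is a national income label, which says little about asset scores among inpatients. Each country also contributes a central and a district hospital, so the spread within country may be wide.

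A reader might also take the utility gap as the bias in the reported HRQoL result. It is about four times the corresponding 90-day QALY figure. A constant offset would also cancel in a simple change from admission among survivors, though not in an area-under-the-curve QALY. Nor does the illustration show that a true gradient would vanish or reverse.

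**Conclusion.** The point holds in conditional form. If quintiles are pooled and the models have no country or site term, contrasts between quintiles on cost and QALYs are confounded with country at any non-zero difference in asset wealth between the countries, provided the outcome also differs by country.

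The confounding is modest at a small wealth gap and material at 0.5 to 1.0 SD, where the extreme quintiles differ by 34 to 63 percentage points in country mix. The corresponding spurious difference of about 0.008 to 0.016 QALY depends entirely on the assumed 0.10 tariff offset and equal recruitment. The article itself expects recruitment to vary by site. These figures show the mechanism and are not forecasts for this study. The matter is worth correcting because it bears on a stated socioeconomic aim and the remedy is simple.

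**What to change.** In the Phase 1B analysis, where the wealth score is defined, state one of two rules: scores and quintiles are built separately within each country, or the DHS-referenced national quintiles already planned are the exposure in every comparison of cost, clinical outcome and HRQoL. Where the cost and HRQoL comparisons are described, add country or site as a model term. That term is needed with the DHS-referenced version in particular, because external cut points do not guarantee an equal country mix in each quintile.

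The cost is a few words of analysis text. The asset data and the national quintiles are already planned, and Study status says that the analysis has not been performed and the code is still being written. The small downside is one of interpretation: within-country quintiles measure relative rather than absolute wealth across the two countries, and the report should say so. If within-country construction is already intended, one sentence settles the matter.
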